## Abstract

**Background:**

Anterior open treatment of the inguinal hernia with a tension-free mesh has reduced the incidence of hernia recurrence. The Lichtenstein procedure is the current reference technique for inguinal hernia treatment. Chronic pain has become the main postoperative complication after surgical inguinal hernia repair, especially following Lichtenstein. Preliminary experiences with a soft mesh positioned in the preperitoneal space (PPS) by transinguinal preperitoneal (TIPP) or total extraperitoneal (TEP) technique, showed promising results considering the reduction of postoperative chronic pain. Evolution of surgical innovations for inguinal hernia repair led to an open, direct approach with preperitoneal mesh position, such as TIPP. Based on the TIPP procedure, another preperitoneal repair has been recently developed, the transrectus sheath preperitoneal (TREPP) mesh repair.

**Methods:**

The ENTREPPMENT trial is a multicentre randomized clinical trial. Patients will be randomly allocated to anterior inguinal hernia repair according to the TREPP mesh repair or TIPP procedure. All patients with a primary unilateral inguinal hernia, eligible for operation, will be invited to participate in the trial. The primary outcome measure will be the number of patients with postoperative chronic pain. Secondary outcome measures will be serious adverse events (SAEs), including recurrence, hemorrhage, return to daily activities (for example work), operative time and hospital stay. Alongside the trial health status, an economic evaluation will be performed. To demonstrate that inguinal hernia repair according to the TREPP technique reduces the percentage of patients with postoperative chronic pain from 12% to <6%, a sample size of 800 patients is required (two-sided test, α = 0.05, 80% power).The ENTREPPMENT trial aims to evaluate the TREPP and TIPP procedures from patients’ perspective. It is hypothesized that the TREPP technique may reduce the number of patients with any form of postoperative chronic pain by 50% compared to the TIPP procedure.

**Trial registration:**

Current Controlled Trials:
ISRCTN18591339

## Background

An inguinal hernia has been reported as a common surgical problem. In The Netherlands, approximately 30,000 inguinal hernia repairs are performed each year
[1]. Tension-free mesh repair has reduced the incidence of recurrence (<5%)
[2]. However, postoperative chronic pain after inguinal hernia repair is the main complication, especially following Lichtenstein procedure
[3-5]. Lichtenstein is the current reference technique for inguinal hernia repair
[6]. The incidence of chronic pain and (hypothetical) pathophysiological mechanisms of chronic pain have been reported. Studies have shown possible advantages in preperitoneal mesh positioning, due to the lack of need for fixating the mesh. Furthermore, the approach in which the inguinal region with its nerves is completely avoided during dissection resulted in less patients with postoperative chronic pain
[7,8]. The effect of the preperitoneal mesh position is in line with those reported after total extraperitoneal (TEP) and transabdominal preperitoneal (TAPP) procedures.

The transinguinal preperitoneal (TIPP) procedure has been described as an alternative open preperitoneal mesh repair
[9,10]. Results of the TULIP trial, comparing TIPP with the Lichtenstein procedure, concluded significantly less patients with postoperative chronic pain after TIPP in the first postoperative year
[11]. Based on the TULIP trial results and the low risk of bias methodology, the TIPP procedure will be used as the control intervention in this trial.

Based on the TIPP procedure, another open preperitoneal mesh repair has been developed, the transrectus sheath preperitoneal (TREPP) mesh repair. Description of the technique and results of the first 50 TREPP cases have been reported
[12]. This pilot study showed promising results for TREPP. The TREPP principles are: an open technique, easy to learn, sutureless preperitoneal mesh position, and avoiding the inguinal canal and inguinal nerves peroperatively. These principles are in concordance with the reported recommendations of Reinpold
[13].

The aim of this randomized clinical trial is to evaluate the TREPP and TIPP procedures. The trial design focuses on the three dimensions of possible errors: bias, the ‘play of chance’ and the chosen outcome
[14-16].

## Methods

Prior to the start of the trial, the study protocol was written and will be published. The ENTREPPMENT trial is registered with the International Standard Randomised Controlled Trial Number (ISRCTN) Register (
http://controlled-trials.com/ISRCTN18591339). The protocol was ethically approved by the official Independent Review Board Nijmegen (2012/060) and registered nationally (NL38842.091.12)
[17].

### Design

The ENTREPPMENT trial will be a prospective randomized multicentre trial. Two inguinal hernia repair techniques, TREPP and TIPP, will be compared.

Patients will be included at the outpatient clinics of the participating centers (Radboud University Nijmegen Medical Centre, Nijmegen; St Elisabeth Hospital, Tilburg; TweeSteden Hospital, Tilburg/Waalwijk; Gelderse Vallei Hospital, Ede; and St Jansdal Hospital, Harderwijk) by surgeons and supervised residents.

Prior to the start of the trial, group sessions in the operation room (and by discussion) for complete standardization and uniformity of the TREPP and TIPP procedures will be performed with the participating surgeons. All surgeons will be assessed by an experienced colleague (proctor) prior to their participation in the trial. The proctors will decide whether the surgeon has completed the learning curves of both techniques and can start the procedures in the trial.

Randomized patients will be operated on according to this protocol. Dedicated hernia surgeons will perform the operations or will supervise the residents. The same mesh with memory ring will be used in both techniques (Polysoft 16 × 9.5cm; Bard, Benelux, Belgium). The skin will be closed intracutaneously.

### Patients

Patients with a primary unilateral inguinal hernia, visiting the outpatient clinics at the participating centers will be invited to participate.

Inclusion criteria are: primary unilateral groin hernia, aged between 18 and 80 years, American Society of Anesthesiologists’ (ASA) classification 1 to 3, and signed informed consent.

Exclusion criteria are: recurrent inguinal hernia, scrotal hernia, femoral hernia, acute incarcerated inguinal hernia, psychiatric disease, or other reasons making follow-up or questionnaires unreliable, and previous preperitoneal surgery, for example radical prostatectomy.

### Intervention

The TREPP technique has been described
[12]. To reach the preperitoneal space (PPS), a 5 cm transverse incision is made approximately 1 cm cranial to the pubic bone. The anterior rectus sheath is opened by transverse incision. After retraction of the muscle fibers medially, the inferior epigastric vein and artery are identified and retracted medially. The underlying transverse fascia is opened transversely as well. With a gentle movement, the PPS is dissected and a medial hernia may be reduced immediately. Using the iliac vessels as a landmark, the funiculus is identified with the spermatic cord, the testicular vessels and a possible lateral hernia. The latter (if present) may now be reduced. Using three long and thin retractors, a perfect overview of the PPS may be achieved and all possible hernia orifices (medial, lateral and/or femoral) can be visualized. The soft mesh is positioned in the PPS and covers the complete myopectineal orifice of Fruchaud. After deployment, the abdominal pressure keeps the mesh in position without necessitating any fixation. The anterior rectus sheath and the fascia of Scarpa are closed with Vicryl (Ethicon, Livingston, UK).

### Control intervention

The TIPP procedure has been described by Pelissier
[9,10] and evaluated in the TULIP trial
[18]. In brief, using the transinguinal approach, nerves will be identified and spared. The hernia sac is reduced into the PPS. The PPS is dissected bluntly by a finger. A soft mesh with memory ring is positioned in the PPS without the need for fixation.

### Outcome measures

The primary outcome measure will be the number of patients with postoperative chronic pain. Chronic pain is defined by the International Association for the Study of Pain as any visual analog scale (VAS) score above zero that lasts for more than 3 months postoperatively
[19]. To prevent the disadvantages of a single measurement, postoperative chronic pain will be assessed at 6 and 12 months.

Secondary outcome measures are serious adverse events (SAEs) during the first year after randomization. SAEs are: death, irrespective of the cause; life-threatening event; re-admission to the hospital; hemorrhage; wound infection, either surgical site or deep infection; and recurrence (symptomatic) of the inguinal hernia. When in doubt considering the seriousness of an event, a blinded expert opinion will be obtained.

Other secondary outcome measures will be hospital stay, operative time, numbness and return to daily activities. Alongside the trial, an economic evaluation and the health status will be assessed.

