### Ethics and informed consent

This study is conducted in concordance with the principles of the Declaration of Helsinki
[22] and Good Clinical Practice guidelines. The protocol was ethically approved by the official Independent Review Board Nijmegen (2012/060) and registered nationally (NL38842.091.12)
[17]. A Data and Safety Monitoring Board (DSMB) is established to perform safety surveillance and to perform interim analyses on the safety data, as described.

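### The six-item SAE list has no entry for complication-related prolongation of the index stay, re-operation before discharge, non-bleeding operative organ injury or lasting disability, so these harms may not be counted as SAEs in either arm

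*Protocol article*

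**What the plan says.** The protocol article, Outcome measures, sets both the safety outcome and its window: "Secondary outcome measures are serious adverse events (SAEs) during the first year after randomization". It then defines the term by a list: "SAEs are: death, irrespective of the cause; life-threatening event; re-admission to the hospital; hemorrhage; wound infection, either surgical site or deep infection", closing with "recurrence (symptomatic) of the inguinal hernia". That makes six entries.

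One sentence follows on borderline cases: "When in doubt considering the seriousness of an event, a blinded expert opinion will be obtained". The remaining clinical outcomes come next: "Other secondary outcome measures will be hospital stay, operative time, numbness and return to daily activities".

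The abstract is looser: "Secondary outcome measures will be serious adverse events (SAEs), including recurrence, hemorrhage", and the same sentence continues into return to activities, operative time and hospital stay.

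Three other sections bear on the point:

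- Intervention describes the TREPP dissection: "Using the iliac vessels as a landmark, the funiculus is identified with the spermatic cord, the testicular vessels and a possible lateral hernia".
- Randomization and blinding keeps operation reports blinded in the patient file and closes them to outcome assessors.
- Ethics and informed consent sets up a monitoring board that "is established to perform safety surveillance and to perform interim analyses on the safety data".

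**The concern.** SAEs are the trial's main listed safety comparison. The window opens at randomization, and allocation is obtained just before incision, so the index operation and admission lie inside it. Yet the list is thin for exactly that period. A patient who stays longer because of a complication, is re-operated on before going home, has an organ injury repaired without bleeding, or is left with a permanent loss managed without admission meets no entry.

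The two operations reach the preperitoneal space by different routes, so a comparison of operative harm is of real interest. If such events are not counted in either arm, the SAE comparison cannot show a difference between the arms in them, and similar SAE rates would say nothing about these harms.

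**Working it through.** The article gives no rate for any of these events, so there is no stated figure to reproduce. The check is a reading of the list against each type of event.

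**Step 1. Entries that can apply during the index admission.** Re-admission cannot, because it presupposes discharge. Symptomatic recurrence is normally a later event. Four entries remain: death, threat to life, bleeding and wound infection.

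**Step 2. Event types against the six entries.**

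| Event | Entry that applies directly | Counted only if it also… |
|---|---|---|
| Index stay prolonged by a complication | none | bleeds, is a wound infection, or threatens life |
| Re-operation before discharge | none | is done for bleeding or wound infection, or threatens life |
| Operative organ injury, no bleeding, no threat to life | none | leads to wound infection or re-admission |
| Operative vessel injury | hemorrhage, where it bleeds | – |
| Lasting disability or organ loss | none | leads to re-admission or meets another entry |

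**Step 3. Other routes by which these events might be admitted.**

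- *Blinded expert.* The clause deals with doubt about seriousness. It names no criterion and adds no category, and someone must first have raised the event.
- *Abstract.* Its sentence runs straight on to return to activities, operative time and hospital stay. Outcome measures classes these as other secondary outcomes, not SAEs. The sentence is therefore a compressed list of secondary outcomes and does not clearly open the SAE definition.
- *Hospital stay and operative time.* Both are durations. Under Statistics, continuous outcomes are analysed by covariance analysis with centre, after log transformation if skewed. A few long values caused by complications are damped, and their cause is not identified.
- *Physical examination at 14 days, 6 months and 1 year.* This could reveal a late loss, but observing it does not make it an SAE without an entry.

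No route clearly admits the events.

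**Step 4. Illustration of scale, with assumed rates.** Enrolment is 800 (Analysis and sample size). Assuming 1:1 allocation, which the article does not state, each arm has 800 / 2 = 400. For an unlisted harm with true rate p, the expected count in an arm is 400p and the chance of at least one event is 1 − (1 − p)^400:

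- p = 0.5%: 2 events expected; chance of at least one 87%
- p = 1%: 4 events expected; chance 98%
- p = 2%: 8 events expected; chance above 99%

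At such rates some events would probably occur. Counting them would not by itself guarantee a significant contrast. For 4 against 0 in 400 per arm, the two-sided Fisher p is 2 × (400·399·398·397)/(800·799·798·797) = 2 × 0.0620 ≈ 0.12. The value of listing them lies in complete reporting and in an interval estimate for the difference.

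**The case against.** The strongest reply is that the article condenses a fuller protocol. The trial is run under Good Clinical Practice with a monitoring board, and adverse-event definitions and form fields usually sit in the full document. The expert clause would also be most useful for events not plainly on the list, and the abstract's wording sounds open. Part of this stands: wider adverse-event reporting may well exist, and it is not certain that the events would be lost. But the article does not leave the SAE outcome undefined. It prints a definition, and wider reporting elsewhere would not change the outcome as printed.

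Partial capture is also real. Vessel injury would often enter as hemorrhage, later consequences as re-admission, and repair time or a longer stay would lengthen two recorded durations. This narrows the gap without closing it.

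Several stronger readings are tempting, and the article does not support them:

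- A reader might infer that these harms will certainly go uncounted. The expert clause leaves that open.
- A reader might infer that the gap favours TREPP. The same list applies to both arms, TIPP also dissects the preperitoneal space, and the Intervention section reports no injury. It shows only that the approach works close to vessels and cord.
- A reader might infer that minor infections will dominate the SAE count. No infection rate is given, and recurrence, the sixth entry, is the only one with a figure (below 5% after mesh repair, Background).
- A reader might infer that the monitoring board sees only these six items. It is said to review safety data, with no such limit.

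Reporting superficial infection separately, or adding conversion as an outcome, would be a preference and not the correction of a fault.

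**Conclusion.** The point holds in a limited form. As printed, the SAE outcome has no entry for complication-related prolongation of the index stay, re-operation before discharge, operative organ injury that neither bleeds nor threatens life, or lasting disability or organ loss. No written criterion tells the blinded expert to admit them. In either arm they may therefore not be counted as SAEs, and a difference between the techniques in these harms could be missed.

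The size cannot be estimated from the article. The counts above rest on assumed rates of 0.5% to 2% and on 1:1 allocation. The conclusion also assumes that the printed list is the operative definition. The primary outcome, sample size and main analysis are not affected.

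**What to change.** Add four entries to the SAE list in Outcome measures:

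1. prolongation of the index stay because of a complication;
2. re-operation at any time, including before discharge;
3. intra-operative organ or vessel injury;
4. persistent disability or organ loss, including testicular loss.

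State that the blinded expert judges seriousness against these criteria as well as the existing ones.

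Because outcome assessors may not see operation reports, intra-operative events need their own route. The operating team should record them on a separate form that does not disclose the technique to the assessors.

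The cost is somewhat more SAE reports and a small extra form. Trial status says inclusion has not started, so the change can be in place for every patient.

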### Anesthesia and analgesia

Preoperatively, all patients will visit the anesthesiologist. One analgesia protocol will be used in combination with a standardized regimen regarding both postoperative pain and nausea medication. These regimes are based on daily practice; the standardization serves to avoid unnecessary bias. First choice of anesthesia technique is spinal anesthesia, owing to its ease and expedited postoperative recovery, avoiding the risks of general anesthesia (nausea, tube, aspiration, heart/lung complications). If the patient declines, general anesthesia will be permitted. All anesthesiologists will be experienced with both general and spinal anesthesia. The wound will be infiltrated with 10 cc bupivacaine 0.1%.

### Randomization and blinding

The randomization will be stratified by centre. Correct generation of the allocation sequence, allocation concealment, blinding and follow-up will be warranted. The allocation sequence will be computer-generated. The trial office will be contacted online prior to incision. The nurse in the operating room will write down the technique for the surgeon, so the patient will be unaware of the technique used. Operation reports will be blinded in the electronic patient files and no access will be allowed for the outcome assessors. Plasters will be positioned identically after both techniques. During follow-up, questionnaires will be completed before contact with outcome assessors and physical examination, to provide optimal masking.

### Unblinding protocol

Patients will be informed on request about the performed procedure only after completing the last follow-up visit.

### Data recording and follow-up

All hernias will be classified according to the European Hernia Society (EHS) hernia classification (Figure 
1)
[20].

**Figure 1 F1:**
[figure not shown]
**European Hernia Society (EHS) groin hernia classification ****[**[20]**].**

All included patients will be interviewed preoperatively according to the Pain Disability Index (PDI), Short Form 36 (SF-36) and EQ-5D. Preoperative pain scores will be assessed by the Verbal Rating Scale (VRS) for pain. All patients will keep a pain diary including the PDI and the VRS for pain during the first 14 postoperative days.

The pinprick-test will be used to assess numbness in the dermatomes related to the inguinal nerves on the operated side. A figure of dermatomes will be used for anatomical orientation
[21].

Follow-up, including the three questionnaires and a physical examination, will be scheduled at 14 days, 6 months and 1 year postoperatively.

### Ethics and informed consent

This study is conducted in concordance with the principles of the Declaration of Helsinki
[22] and Good Clinical Practice guidelines. The protocol was ethically approved by the official Independent Review Board Nijmegen (2012/060) and registered nationally (NL38842.091.12)
[17]. A Data and Safety Monitoring Board (DSMB) is established to perform safety surveillance and to perform interim analyses on the safety data, as described.

### Analysis and sample size

It is hypothesized that the TREPP technique reduces the percentage of patients with any form of postoperative chronic pain from 12% to 6%, or less. The TULIP trial shows an incidence of patients with any form of postoperative chronic pain, either continuous or pain during activity, of 12%. Step-up studies show postoperative chronic pain after the TREPP technique, self-monitored by patients and measured by a non-validated questionnaire, of 7% in a large undefined group.

Based on an absolute risk reduction from 12% to 6%, a sample size of 720 patients is required (two-sided test, α = 0.05, 80% power).

In order to compensate for possible loss to follow-up, 800 patients will be enrolled. The study end is expected 2.5 years after the start of the trial: 1.5 years of inclusion and 1 year of follow-up. No interim analyses will be planned.

### Statistics

The analysis will be performed on the basis of the intention-to-treat principle. Logistic regression with centre as cofactor will be used to analyze binary outcomes. Similarly, analysis of covariance with centre as factor will be used to analyze continuous outcomes. Skewed variables will be log transformed. A two-sided *P* value of <0.05 will be considered to be significant and 95% confidence intervals will be calculated.

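### The planned analysis of covariance names no covariate: baseline PDI, SF-36 and EQ-5D are collected but left out of the stated model, at some cost in precision

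*Protocol article*

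**What the plan says.** The Statistics section of the protocol article fixes two models. For binary outcomes: "Logistic regression with centre as cofactor will be used to analyze binary outcomes". For continuous outcomes: "analysis of covariance with centre as factor will be used to analyze continuous outcomes". Neither sentence names any adjustment term other than centre. Centre is also the stratification factor: "The randomization will be stratified by centre" (Randomization and blinding).

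The text on data recording and follow-up, after the hernia classification figure, describes the baseline data: "All included patients will be interviewed preoperatively according to the Pain Disability Index (PDI), Short Form 36 (SF-36) and EQ-5D". It adds: "Preoperative pain scores will be assessed by the Verbal Rating Scale (VRS) for pain". The same instruments come back after surgery: "Follow-up, including the three questionnaires and a physical examination, will be scheduled at 14 days, 6 months and 1 year postoperatively".

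Under Outcome measures, "The primary outcome measure will be the number of patients with postoperative chronic pain". That outcome is defined there by a VAS score above zero persisting beyond 3 months. Operative time, hospital stay and return to activities are among the secondary outcomes. Health status and an economic evaluation are assessed alongside the trial.

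**The concern.** An analysis of covariance is an analysis of variance with at least one continuous covariate. The only term named here besides treatment is centre, which is categorical, so the model as described is a two-way analysis of variance of follow-up scores. Either the label is loose or the intended covariate was not written down.

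Three instruments are measured on every patient before surgery and again on the same scales afterwards. The preoperative score on a scale usually predicts the later score on it. Leaving it out puts that predictable variation into the residual and widens the interval for the treatment difference in PDI, SF-36 and EQ-5D. It also leaves a reader unsure whether the baseline will be used, and that choice should be settled before data are seen.

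The same question arises, with less force, for preoperative pain in the logistic model for chronic pain.

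**Working it through.** **1. The plan's own figure.** Inputs from Analysis and sample size: 12% versus 6%, two-sided α = 0.05, 80% power. Equal allocation is assumed. With pooled variance and mean proportion 0.09:

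n per arm = [1.96·√(2·0.09·0.91) + 0.8416·√(0.12·0.88 + 0.06·0.94)]² / 0.06² = 356, so 712 in total.

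The unpooled version gives 354 per arm, 708 in total. Both agree with the stated 720 to within rounding, and 720/0.9 = 800 matches the planned enrolment. The sample size rests on the binary outcome, and this point does not change it.

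**2. Scores with a baseline (PDI, SF-36, EQ-5D).** Let r be the correlation between the baseline and follow-up score on the same scale. Adjusting for baseline multiplies the residual variance by 1 − r² and the interval width by √(1 − r²). Omitting it therefore widens the interval by the factor 1/√(1 − r²). The documents give neither r nor any standard deviation, so r is an assumed range. With 720 patients analysed, 360 per arm:

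| Assumed r | Variance factor 1 − r² | Width factor with baseline | Interval wider without baseline | Unadjusted patients equivalent to 720 adjusted |
|---|---|---|---|---|
| 0.3 | 0.91 | 0.954 | 1/0.954 = 1.05, about 5% | 720/0.91 = 791 |
| 0.5 | 0.75 | 0.866 | 1/0.866 = 1.15, about 15% | 720/0.75 = 960 |
| 0.7 | 0.51 | 0.714 | 1/0.714 = 1.40, about 40% | 720/0.51 = 1412 |

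In terms of power, the difference detectable with 80% power without the baseline is (1.96 + 0.8416)·√(2/360) = 0.209 SD. With the baseline in the model, power for that same difference is about 84%, 90% and 97.5% for r = 0.3, 0.5 and 0.7. The 0.209 SD is only a reference value; the plan sets no target for these scores.

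**3. Primary outcome.** This was checked by simulating logistic regression: 3,000 trials per scenario, 360 per arm, five centres of equal expected size with no centre effect, marginal risks of 12% and 6%, and one continuous baseline covariate. The covariate's odds ratio per SD is assumed.

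| Assumed odds ratio per SD | Power, arm + centre | Power, arm + centre + baseline |
|---|---|---|
| 1 | 80.9% | 80.8% |
| 1.5 | 80.6% | 80.7% |
| 2 | 80.8% | 82.4% |
| 3 | 81.0% | 84.5% |

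The simulation standard error of each figure is √(0.8·0.2/3000), about 0.7 points, so the first two rows show no gain. The range is about 0 to 3.5 points. A verbal rating scale is coarser than the continuous covariate simulated here.

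**The case against.** The strongest reply is that the article does not say centre is the only term. A named analysis of covariance with centre added as a factor could imply covariates that the full protocol or analysis plan lists, and an article may leave such detail out. The possibility stands. It does not dispose of the point, because the article states its adjustment terms instead of deferring them, and the one term it gives for the continuous model is not a covariate.

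Other objections stand and limit the point:

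- **Validity.** A reader might infer that the centre-only analysis is biased, or that chance imbalance in preoperative pain undermines the primary comparison. The documents do not support this. Allocation is randomised, the model respects the stratification factor, and chance imbalance is already covered by the type I error rate and the confidence interval.
- **Scope.** A reader might extend the loss to every continuous outcome. Operative time, hospital stay and return to activities have no preoperative value, so no baseline term can be fitted for them.
- **Primary outcome.** A reader might conclude that the primary analysis loses precision or is underpowered. In logistic regression, adding a prognostic covariate does not shrink the standard error of the log odds ratio. It changes the target to a conditional odds ratio, with slightly more power. Without the covariate, power in the simulation is still about 81%.
- **Scale.** A preoperative pain covariate on the scale of the outcome is not available from the data described: preoperative pain is on the VRS, and chronic pain is defined by the VAS.

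**Conclusion.** The point holds as one of efficiency and wording, mainly for PDI, SF-36 and EQ-5D. The stated model is valid, but it carries a name that implies a covariate, specifies none, and leaves unused the baseline scores the trial collects. The cost is an interval about 5%, 15% or 40% wider for r = 0.3, 0.5 or 0.7. These correlations are assumptions; the direction of the effect is not in doubt, but its size cannot be read from the documents.

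For the primary outcome the case is optional. The gain is about 0 to 3.5 percentage points of power for assumed odds ratios of 1 to 3 per SD, and it is nil at the lower end. Nothing here calls the sample size or the primary conclusion into question. Label: free improvement.

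**What to change.** In the Statistics section, state that PDI, SF-36 and EQ-5D scores will be analysed by ANCOVA with arm, centre and the preoperative value of the same scale, and that continuous outcomes without a preoperative value (operative time, hospital stay, return to activities) will be analysed with arm and centre.

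Optionally, state that the logistic model for chronic pain will include arm, centre and the preoperative VRS pain score as collected. A VAS baseline should not be specified, since the article does not describe one. If this term is added, the odds ratio becomes conditional on baseline pain as well as centre, so the marginal risk difference should be reported beside it, in keeping with the 12% versus 6% on which the trial is sized.

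The cost is one or two sentences. No new data and no additional patients are needed. The Trial status section says recruitment had not begun, so the change can be prespecified cleanly.
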